## Abstract

**Background:**

School interventions such as the Incredible Years *Classroom *Dinosaur Programme targets pupil behaviour across whole classrooms, yet for some children a more intense approach is needed. The Incredible Years *Therapeutic *Dinosaur Programme is effective for clinically referred children by enhancing social, problem-solving skills, and peer relationship-building skills when delivered in a clinical setting in small groups.

The aim of this trial is to evaluate the effectiveness of the Therapeutic Programme, delivered with small groups of children at high-risk of developing conduct disorder, delivered in schools already implementing the Classroom Programme.

**Methods/Design:**

This is a pragmatic, parallel, randomised controlled trial.

Two hundred and forty children (aged 4-8 years) rated by their teacher as above the 'borderline cut-off' for concern on the Strengths and Difficulties Questionnaire, and their parents, will be recruited.

Randomisation is by individual within blocks (schools); 1:1 ratio, intervention to waiting list control.

Twenty schools will participate in two phases. Two teachers per school will deliver the programme to six intervention children for 2-hours/week for 18 weeks between baseline and first follow-up. The control children will receive the intervention after first follow up.

Phase 1 comprises three data collection points - baseline and two follow-ups eight months apart. Phase 2 includes baseline and first follow-up.

The Therapeutic Programme includes elements on; Learning school rules; understanding, identifying, and articulating feelings; problem solving; anger management; how to be friendly; how to do your best in school.

Primary outcomes are; change in child social, emotional and behavioural difficulties. Secondary outcomes are; teacher and parent mental wellbeing, child academic attainment, child and teacher school attendance. Intervention delivery will be assessed for fidelity.

Intention to treat analyses will be conducted. ANCOVA, effect sizes, mediator and moderator analyses will be applied to establish differences between conditions, and for whom the intervention works best for and why.

**Discussion:**

This trial will provide information on the delivery and effectiveness of a child centred, school-based intervention delivered in small groups of children, at risk of developing more severe conduct problems. The effects on child behaviour in school and home environments, academic attainment, peer interactions, parent and teacher mental health will be assessed.

**Trial Registration:**

UK Clinical Research Network UKCRNID8615

Current Controlled Trials ISRCTN96803379

## Background

Social and emotional wellbeing can be defined as being happy and confident, autonomous, attentive, resilient, and possessing the ability to foster good relationships and solve problems. Barriers to wellbeing are depression and antisocial behaviour [1]. Children who display early signs of anti-social behaviour and conduct problems are at high risk of early onset conduct disorder (CD). CD constitutes the largest single group of psychiatric disorders in children and adolescents and is the main reason for referral to Child and Adolescent Mental Health Services (CAMHS) [2]. Children with early onset problems are at high risk of low school attendance, educational underachievement, school dropout [3] and subsequent mental health problems [4].

Living in poverty in poor quality housing, having young and/or single parents, living with adults with unemployment or mental health problems increases the probability that children will arrive at school with social and emotional skill deficits [5]. Additional risk factors associated with higher prevalence for CD include, frequent changes of parental figures, parental psychopathology, parental substance abuse, marital problems, and poor parenting skills [6].

The Incredible Years (IY) series developed over the last 30 years, comprises a suite of programmes, for parents, children and teachers, with strong evidence of effectiveness both as treatment programmes for children with CD and as early preventive programmes (for more information on programmes and research see: http://www.incredibleyears.com). IY was one of the eleven programmes deemed a 'blueprint' programme for violence prevention following a rigorous review of 600 interventions [7]. The Incredible Years Series has a strong evidence base in Wales and is acceptable to families and schools [8-10].

Parenting programmes are very effective in developing children's social skills and reducing child behavioural problems [4,8,10-13] whilst reducing later burden on social, health, education service use and associated costs and the costs of lifetime unemployment and welfare dependence [14-17].

Limitations of parenting programmes are that improvements at home do not always transfer to school settings [18,19] with programme provision limited to the few families that can, or are willing to, access programmes. Schools are therefore dealing with significant numbers of children with behavioural and self-regulatory difficulties particularly in disadvantaged areas where levels of CD reach 35% [2,20].

In Wales initial steps to tackle the increasing numbers of children arriving in school with social, emotional and behavioural difficulties have been taken; there has been a change in the curriculum of early years education and a commitment to improve home-school partnerships [21]. Gwynedd Education Service in North Wales has implemented and established the universal IY Classroom Dinosaur curriculum in all of their 102 primary schools; however high-risk children need additional input to meet their needs. The IY Therapeutic Dina Programme [22] has been successful in increasing social and emotional competence in high-risk children by increasing social and problem-solving skills, and by strengthening peer relationships in clinical settings [23] and in a small pilot study in Wales [9].

The IY Therapeutic Programme would be ideally placed within schools, where children who would benefit form the programme could be easily identified by teachers. Teachers are best placed to deliver the programme to the children in schools, and to encourage the completion of the programme's homework tasks by children with their parent/s. School-to-home links will be forged through discussion of homework tasks.

### Summary of background literature

• Fostering social and emotional competency can reduce or prevent CD, which is prevalent in disadvantaged areas such as North Wales

• Parent programmes are beneficial but more support is needed for children in school, as behaviour 'rules' learnt in the home may not generalise to school

• Schools are an ideal arena for targeting difficult child behaviour and increasing positive behaviour whilst strengthening school-home links

• All 102 primary schools in Gwynedd implement IY programmes (Teacher Classroom Management and Classroom Dinosaur)

• The intensive IY Therapeutic Programme with high-risk children in schools may benefit children for whom the IY Classroom Dinosaur is insufficient

### The rationale for the trial

The aim of this paper is to present the research protocol for the randomised controlled trial (RCT) designed to primarily establish whether the IY Therapeutic Dinosaur School Programme, when delivered as a school-based targeted intervention, improves 'at risk' children's social, emotional and behavioural competencies compared with a waiting list control condition.

#### Secondary questions include

1. For which children is the intervention most effective?

2. What are the environmental/contextual circumstances that improve the likelihood of success?

3. Does behaviour change in school generalise to the home?

4. Does the duration of time participating in an intervention affect the likelihood of success, that is, is there a dosage affect?

5. Can the intervention be implemented efficiently and effectively with fidelity by teachers in mainstream schools?

6. Does the mental health of teachers and parents of the intervention children improve?

## Method and design

This is a 3-year study, beginning in 2010, set in primary schools in Gwynedd, North Wales. It comprises two phases; half of the proposed 20 schools will deliver the programme to the (maximum) six children allocated to intervention condition in Phase 1 (2011), with the remaining schools delivering the intervention in Phase 2 (2012). Each school will deliver the programme (if effective) to the waiting-list control children in the subsequent school year.

Phase 1 comprises three data collection points - baseline and two follow-up points at 8-month intervals. Phase 2 comprises baseline and first follow-up only due to timetabling restrictions (see Additional File 1).

### Participants

Twenty schools will be identified and recruited in conjunction with Gwynedd Education Services.

In total 240 children will participate (120 intervention, 120 control) across the 20 schools. The 240 children, aged 4-8 years will be identified as scoring at least borderline for concern on the total difficulties score of the Teacher Strengths and Difficulties Questionnaire [24].

The primary caretaker or parent (n = 240) will complete measures on themselves and their child.

Teachers with a participating child in their class will complete a brief demographic form and a measure of teacher stress; Teacher sample size will be determined after recruitment of families.

Forty facilitators (teachers, or teachers partnered with classroom assistants), two from each school, will deliver the intervention to the children. The facilitators will be chosen by the school and will have undertaken relevant IY training to enable delivery.

Participant summary:

• 20 schools (10 in each phase)

• 240 children, 12 in each school, 6 intervention and 6 waiting list control

• 240 parents (primary caretaker of child participants)

• Teachers (of participant children, n = TBC following recruitment of families)

• 40 facilitators (teachers and classroom assistants)

See Additional File 2 for the Consort diagram of flow of participants.

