#### Secondary outcome measures

For children:

• The Eyberg Child Behaviour Inventory across all time points is a 36-item inventory, completed by the parent for the assessment of frequency and intensity of behavioural problems in children aged 2-16 years [25]. A high score in each of the subscales denotes more frequent/intense problem behaviour.

• The Bangor Dinosaur School Questionnaire has been developed by [name] [26], to assess levels of social and emotional competence. A high score denotes higher rates of social/emotional competence.

• The Wally Problem Solving test assesses children's problem-solving skills and solution types (positive and negative) in response to hypothetical problem situations http://www.incredibleyears.com.

• Blind observation of peer interaction to assess friendship skills (observation tool under development)

• Child interview to ascertain number of friends a child has

• Academic attainment - assessed by school records

• School attendance - assessed by school records

For parents (self-reports):

• The Parenting Scale questionnaire [27] is a 30-item inventory is designed to measure dysfunctional discipline practices in parents of children aged 1.5 to 4 years, but has been used successfully in older children up to age sixteen [8]. A high score denotes high rates of dysfunctional practices.

• The Beck Depression Inventory [28] is a 21-item measure to assess the severity of characteristic attitudes and symptoms associated with depression. A high score relates to increased levels of depression.

• The Warwick-Edinburgh Mental Well-being Scale (WEMWBS) [29] is a 14-item positively worded measure assessing mental health. The higher the score the higher the levels of well-being.

For teachers (self-report):

• The Teacher Stress Inventory (TSI) [30] is a 20-item measure to examine the effect of difficult classes, impolite pupils and maintaining class discipline on teacher stress levels. The higher the score the higher the stress levels.

Additional measures relating to programme delivery and child responsiveness consist of:

• Implementation fidelity checks - facilitator-completed after each week's session has been delivered

• Child Dina homework completion rates - facilitator assessed

• Attendance levels of child at Dina group - facilitator assessed

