### Data Collection

Parent measures will be completed during home visits by the research team. A £10 cash incentive will be paid to the parent at the end of each data collection visit on completion of measures.

Teacher measures will be completed independently during school time and collected by researchers.

Child data will be collected by researchers during school time, by prior arrangement with the schools.

Research staff will be trained in the observational tool until 70% inter-rater reliability is obtained. At least 20% of 'blind' observations will occur with two researchers to gauge inter-rater reliability. Frequent practice and trouble-shooting meetings will be held to maintain reliability levels.

Facilitator implementation checklists and child programme attendance will be collected after each weekly Dina session.

Teacher and child attendance levels will be collected for each term. Child academic attainment, by means of expected and achieved grades, will be collected at each time point from Gwynedd Education Central database, or requested through individual schools.

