### Randomisation

This is a pragmatic, parallel, RCT, with children individually randomised on a 1:1 basis, intervention or waiting-list control.

Individual (child) block randomisation within school will be applied with gender as the stratification variable. The North Wales Organisation for Randomised Trials (NWORTH), an independent registered trials unit, will perform the randomisation process using a computer programme written specifically for this trial. Randomisation will occur after eligibility has been established, informed consent obtained and baseline measures collected from parents.

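### Teacher stress and attendance are secondary outcomes, but randomising children within schools gives teachers no condition, so the stated comparison would be diluted or uncontrolled for them

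*Protocol article*

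**What the plan says.** The abstract's Methods/Design section states: "Secondary outcomes are; teacher and parent mental wellbeing, child academic attainment, child and teacher school attendance". Under Secondary outcome measures, the teacher self-report instrument is introduced thus: "The Teacher Stress Inventory (TSI) [30] is a 20-item measure to examine the effect of difficult classes". Data Collection adds: "Teacher and child attendance levels will be collected for each term". The sixth of the secondary questions asks: "Does the mental health of teachers and parents of the intervention children improve". The abstract's Discussion and the main Discussion both say that effects on teacher mental health will be assessed.

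On who is measured, Participants says: "Teachers with a participating child in their class will complete a brief demographic form and a measure of teacher stress". Any teacher with a participating child is therefore included, whichever arm the child is in. Their number is left open: "Teacher sample size will be determined after recruitment of families".

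On allocation, Randomisation describes "children individually randomised on a 1:1 basis" and adds: "Individual (child) block randomisation within school will be applied with gender as the stratification variable". Participants gives 12 children per school, six in each arm.

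Statistical analyses gives one between-condition model: a mixed-model ANCOVA with a random school effect, fixed treatment effect, gender, age or school year, and baseline value. It also says that similarity within the intervention group will be controlled for. It names no class-teacher term and does not say which outcomes it covers. The Statistical summary also lists regressions and correlations in general terms.

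**The concern.** A parent takes the condition of the one index child. A class teacher may have participating pupils in both arms, and then has no condition. The sixth secondary question pairs teachers with parents as though both could be sorted by the child's allocation, but teachers of intervention children and teachers of control children can be the same people.

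Two routes to an answer are open as the article stands. One attaches each teacher's score to each of that teacher's pupils and runs the stated ANCOVA. The same value then enters both arms for every teacher with a mixed set of pupils. The other looks at change over time in teachers who have an intervention child, which has no comparison group. At stake is the article's undertaking on teacher mental health, and the teacher attendance outcome with it. The primary outcome and the child and parent outcomes are not affected by this point.

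**Working it through.** **The plan's own figures.** The article states no sample size, power or effect for teachers. Its 88% power (N = 160 children) concerns the child-level comparison and is not used here.

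**Inputs.** From Participants: 12 children per school, six per arm. From Randomisation: the child is the unit, allocated 1:1 within school. Assumed: k, the number of participating pupils per teacher, and that every set of six children in a school is equally likely to be the intervention group. The second assumption sets aside the gender stratification, which would shift the figures somewhat according to the gender mix of a teacher's pupils.

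**Step 1: how often a teacher has pupils in both arms.** P(both arms) = 1 − 2·C(6,k)/C(12,k).

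| k | Calculation | P(both arms) |
|---|---|---|
| 1 | 1 − 2·6/12 | 0% |
| 2 | 1 − 2·15/66 | 54.5% |
| 3 | 1 − 2·20/220 | 81.8% |
| 4 | 1 − 2·15/495 | 93.9% |
| 6 | 1 − 2·1/924 | 99.8% |

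From k = 7 it is 100%. If the 12 pupils are instead spread at random over an assumed 2, 3, 4, 5, 6 or 8 teachers per school, simulation puts the share of measured teachers whose pupils are all in one arm at about 3%, 16%, 30%, 42%, 50% or 62%. Between 97% and 38% of teachers would then have pupils in both arms.

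**Step 2: what a child-level contrast estimates.** Suppose a teacher's score shifts by δ for each of that teacher's pupils allocated to intervention. For an intervention child, the teacher's expected number of intervention pupils is 1 + (k−1)·5/11. For a control child it is (k−1)·6/11. The difference is 1 − (k−1)/11 = (12−k)/11, so the contrast estimates δ·(12−k)/11.

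| k | (12−k)/11 | Share of δ |
|---|---|---|
| 2 | 10/11 | 91% |
| 3 | 9/11 | 82% |
| 4 | 8/11 | 73% |
| 6 | 6/11 | 55% |
| 12 | 0/11 | 0% |

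**Step 3: whether the test stays valid.** I simulated 20 schools of 6 + 6 children, each child carrying the teacher's score, analysed by least squares with school effects (4,000 runs per setting; assumed SDs 0.5 between schools and 1 between teachers).

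| k | Type I error, δ = 0 | Mean estimate, δ = 0.3 | δ·(12−k)/11 |
|---|---|---|---|
| 2 | 5.0% | 0.274 | 0.273 |
| 3 | 5.3% | 0.245 | 0.245 |
| 4 | 4.7% | 0.218 | 0.218 |
| 6 | 5.1% | 0.164 | 0.164 |

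With no effect, the mean model standard error was within about 2% of the true spread. With δ = 0.3 it was at most about 8% too small (0.0999 against 0.1084 at k = 6).

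**Step 4: the before-after reading.** This needs no arithmetic. Change among teachers who have at least one intervention pupil mixes any programme effect with change over the school year, and no teacher group is named for comparison.

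**The case against.** The strongest reply has four parts.

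First, the ANCOVA text does not name teacher outcomes, its covariates suit children, and the Statistical summary also lists regression, so a child-level ANCOVA of teacher stress is not what the article literally plans. This stands: its use for teachers is an inference from its being the only between-condition model given. The listed regressions do not settle the matter, because no exposure is defined for a teacher.

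Second, unit of analysis and coding are details that an article leaves to the full protocol or SAP. That is true of the model wording. It does not remove the mismatch between the unit randomised and the unit measured, which the design fixes here alongside the undertaking to assess effects.

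Third, a reader might infer that no comparison exists for teachers, that the sixth question cannot be answered for them, or that the child-level standard error is meaningless. The design does not support any of these. Teachers whose pupils are all in one arm can be compared, the number of intervention pupils per teacher varies by chance, the child-level test keeps its nominal error, and dilution is complete only where one teacher has all 12 pupils.

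Fourth, a reader might infer that some measured teachers are also facilitators. The article says only that facilitators are teachers or classroom assistants from the participating schools. Overlap is possible but not documented, and the article does not say whether facilitators are chosen before allocation.

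**Conclusion.** The point holds in a limited form. The article makes teacher stress and attendance secondary outcomes and undertakes to assess effects on teacher mental health, yet its allocation gives no teacher a condition and it does not say how a teacher with pupils in both arms is handled. On the inferred ANCOVA route, the answer is diluted to between 91% and 55% of the per-pupil effect for two to six pupils per teacher. On the before-after route, it is uncontrolled. The size depends on the number of pupils per teacher, on an effect that is linear in the number of intervention pupils, and on a full 6:6 split. With one pupil per teacher the problem disappears. It should be corrected because the remedy uses data already planned, but it concerns secondary outcomes only.

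**What to change.** State that teacher outcomes are analysed with one row per teacher. Regress the follow-up value on the number of that teacher's participating pupils allocated to intervention, conditional on the number participating, with the baseline value and a school effect. Under 1:1 allocation this exposure is random given the number of participating pupils. Add a sensitivity analysis that adjusts for, or excludes, teachers who are facilitators. This should not be part of the main model, because facilitator status might be settled after allocation.

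If this is not wanted, report teacher stress and attendance as uncontrolled description and withdraw the claim to assess effects on teachers.

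The cost is a few lines of analysis text and one model, provided that the link between each pupil and class teacher is kept in the data set. No new measurements are needed. The drawbacks are lower precision, and no information on the exposure from any school where one teacher has all the participants.

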### Recruitment

Research staff will score the Teacher SDQs and inform schools of the initials and dates of birth of the highest scoring eligible children. School staff will initially approach the parents. If interested parents will sign a 'note of interest' form to include contact details and forward to the research team. The research team will telephone the parents to arrange a home visit to discuss the research and recruit the families.

Parents will consent for themselves and on behalf of their child. Consent will be sought at the initial home visit, which will be conducted in the parent's preferred language of Welsh or English. The information and consent forms are available in Welsh and English. The parent will have a week, if required, to decide whether to participate and will be encouraged to discuss participation with their partner, family and friends.

The information sheet also makes explicit that participants, having given their consent, will be free to withdraw their child and themselves from the study at any time without affecting future access to family or children's services. Confidentiality will be assured, unless the researcher has cause for concern regarding child protection issues.

Parents will be informed that their child will be chosen randomly as to whether they receive the intervention in the first or second year of delivery (intervention or waiting list control respectively).

